#### Brief Executive Assessment Tool **(**BEAT) [58]

The BEAT is a screening tool developed to be sensitive to executive dysfunction, particularly in a SUD population. It includes both performance- and inventory-based items. The outcome variable will be total score.

#### Stroop task [59]

In this measure of response inhibition, participants must respond as quickly and accurately as possible across three conditions. The first condition presents the words “red”, “blue”, and “green”; the second presents patches of colours; the third presents words printed in incongruent colours and requires the participant to ignore the word and say the colour. The outcome variable will be total score on the third condition.

#### Five-point test [60]

The Five-Point Test assesses non-verbal figural fluency and consists of producing novel designs under time constraints. The task consists of a sheet of paper with 40 five-dot matrices. Participants are asked to produce as many different figures as possible by connecting the dots within each rectangle within 3 min. The outcome variable will be total designs correctly completed.

#### Alpha span task [61]

The Alpha Span Task is a measure of working memory in which participants are read a list of words and are asked to say the words back in alphabetical order. The outcome variable will be the total alpha score.

#### Symbol Digit Modalities Test (SDMT) [62]

The SDMT is a measure of processing speed in which the participant writes a series of numbers corresponding to symbols according to a symbol-number key at the top of the page. The participant is asked to work through a series of symbols as quickly as they can, with the outcome variable the total number of symbols that can be translated in 90 s.

#### Brief Self-Control Scale (BSCS) [63]

The BSCS is a 13-item self-report questionnaire that assesses individual differences in the construct of self-control. The outcome variable will be total score.

#### EUROQOL – EQ-5D-5L (EQ-5D) [64]

The EQ-5D is a 5-item measure of the quality of life that can be used to calculate Quality Adjusted Life Years in people with Substance Use Disorders. The outcome measure will be total score.

#### EUROHIS-QOL 8-item index (EUROHIS-QOL 8) [65]

The EUROHIS-QOL 8 is an 8-item measure of the quality of life across four domains (physical, psychological, environment, and social). Total QOL score will be the outcome variable.

#### Quality of Life Enjoyment and Satisfaction Questionnaire – Short Form (Q-LES-Q-SF) [66]

The Q-LES-Q-SF is a 16-item self-report questionnaire that assesses quality of life across areas of daily functioning. Total score will be used as the outcome variable.

#### Patient-Reported Outcomes Measurement Information System Global 10 (PROMIS Global 10) [67]

The PROMIS Global-10 consists of 10 items that assess overall perceived quality of life (QOL), including physical health, mental health, social health, pain and fatigue. Total QOL score will be used as the outcome variable.

#### Kessler Psychological Distress Scale Plus (K10+) [68]

The K10+ is a 14-item self-report measure that assesses if a person has been affected by anxiety or depression in the last four weeks. The outcome variable will be total score.

#### Goal Attainment Scaling 2.0 (GAS 2.0) [69]

GAS 2.0 is a revised version of Goal Attainment Scaling (GAS), a technique for quantifying the achievement (or otherwise) of goals set [70]. GAS 2.0 was developed to more objectively determine the level to which a client has attained their goal. Whereas conventional GAS requires the goal setter to estimate the likely outcome (primary goal) in advance, GAS 2.0 derives the primary goal on the basis of: a) current level of functioning and b) maximum realistic level of functioning. It makes use of a goal menu to facilitate and expedite the process of goal setting. The outcome variable will be post-TAU/CR GAS score.

#### Australian Treatment Outcomes Profile (ATOP) [71]

The ATOP is a structured interview that has been validated to measure treatment outcomes in Australian drug and alcohol populations. It contains two sections. Section one details the quantity and frequency of substance use. Section two details health and wellbeing variables such as days in paid work/study, homelessness, eviction risk, violence and arrest, as well as ratings of psychological health, physical health and overall quality of life. This measure will be administered on intake, with participants asked to respond to questions about their substance use, health and wellbeing for the four-week period leading to their commencement of residential rehabilitation. The measure will also be administered at post-discharge follow up, with participants asked to respond to questions about their substance use, health and wellbeing in the previous four weeks.

The following scale will be administered at the end of each session during the CR phase:

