## Abstract

**Background:**

Executive functioning impairment is common in substance use disorder and is a major risk factor for poor treatment outcomes, including treatment drop-out and relapse. Cognitive remediation interventions seek to improve executive functioning and offer a promising approach to increase the efficacy of alcohol and other drug (AOD) treatments and improve long-term therapeutic outcomes. This protocol describes a study funded by the NSW Agency for Clinical Innovation that assesses the effectiveness of delivering a six-week group-based intervention of cognitive remediation in an ecologically valid sample of people attending residential AOD treatment services. We primarily aim to investigate whether cognitive remediation will be effective in improving executive functioning and treatment retention rates. We will also evaluate if cognitive remediation may reduce long-term AOD use and rates of health service utilisation, as well as improve personal goal attainment, quality of life, and client satisfaction with treatment. In addition, the study will involve an economic analysis of the cost of delivering cognitive remediation.

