### The current study

The study will aim to examine the effectiveness of adding a CR intervention to TAU on two primary outcomes, being:A self-report inventory of executive functioning; andTreatment retention

The study will also assess the impact of CR in addition to TAU on a number of secondary outcomes:AOD useHealth service utilisationFunctional goal attainmentQuality of lifeClient satisfaction with treatmentPerformance-based measures of EFEconomic analysis

The study will be conducted as a stepped wedge randomised cluster trial. Stepped wedge designs are increasingly being utilised in the evaluation of interventions within routine treatment services and are recommended where there are limited numbers of clusters [48–50]. The study is funded by the NSW Agency for Clinical Innovation.

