### Assessment measures

See Table 2 for an outline of the timeline of assessment measures. To provide an estimate of the overall level of premorbid intellectual functioning, the Test of Premorbid Functioning [54] will be administered once only, at the first test phase. One primary outcome measure will be an inventory-based measure of EF, as previous findings have shown that inventory-based assessment is more strongly associated with real-world functioning outcomes in SUD than performance-based assessment [36]. Given the high rates of treatment drop-out in residential AOD treatment services, another primary outcome measure will be the length of treatment retention, measured as time in treatment as a proportion of program duration [4]. This is because the program duration may vary across services. Secondary outcome measures will evaluate substance use severity, health service utilisation, individual goal-attainment, quality of life, treatment satisfaction, and performance-based measures of EF. An economic analysis will also be undertaken to evaluate the costs associated with delivering CR versus TAU. Data collection will be facilitated by research assistants blinded to the randomised condition, that is, whether or not a site has implemented cognitive remediation.

**Table 2 Tab2:** Timeline of Assessment Measures

Domain assessment and instrument used	Baseline Assessment	During Intervention	Post-TAU/CR	Follow-Up	Post-trial
Mini International Neuropsychiatric Interview or DSM-V	X				
Drug and Alcohol Cognitive Impairment Screening Tool (DACIST)	X				
Australian Treatment Outcomes Profile (ATOP)	X			X^a^	
Severity of Dependence Scale (SDS)	X		X	X	
Test of Premorbid Functioning	X				
Behaviour Rating Inventory of Executive Functioning – Adult Version (BRIEF-A)	X		X	X	
Kessler Psychological Distress Scale Plus (K10+)	X		X	X	
Quality of Life Enjoyment and Satisfaction Questionnaire – Short Form (Q-LES-Q-SF)	X		X	X	
Patient-Reported Outcomes Measurement Information System Global 10 (PROMIS Global-10)	X		X	X	
Brief Self-Control Scale	X		X	X	
EUROQOL – EQ-5D (EQ-5D)	X		X	X	
EUROHIS-QOL 8	X		X	X	
Q-LES-Q-SF	X		X	X	
Alpha Span Task	X		X	X	
Symbol Digit Modalities Test (SDMT)	X		X	X	
Goal Attainment Scale 2.0 (GAS 2.0)	X		X	X	
Brief Executive Assessment Tool (BEAT)	X		X	X	
Stroop Task	X		X	X	
Five-Point Test	X		X	X	
Group Session Rating Scale		X			
Feasibility/satisfaction questionnaire (staff and clients)					X
Time in Treatment (for individuals)					X

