#### Group Session Rating Scale (GSRS) [72]

The GSRS is a four-item visual analogue scale, designed to be a brief clinical tool to measure group-therapy alliance. The items are presented as bipolar anchors requiring a response on a ten centimetre line. The scale assesses aspects of individual’s perceptions of a group’s therapeutic environment, including; 1) the relationship between the leader and/or group, 2) goals and topics, 3) acceptability of the approach, and 4) overall fit. GSRS scores are obtained by measuring the marks made by the client and summing the lengths to the nearest centimetre on each of the four lines. Scores are summed out of a total possible score of 40. The total score will be the process variable.

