## Discussion

EF impairment is a significant predictor of treatment drop-out for individuals with SUD. There is an opportunity for AOD treatment providers to address cognitive impairment as part of routine care in order to potentially increase treatment efficacy and reduce treatment drop-out. The present study aims to examine the effectiveness of providing a group-based compensatory CR intervention as an adjunct to residential AOD treatment programs. It is expected that compared to pre-intervention, participants will demonstrate a significant improvement in EF and the duration of treatment retention. In addition, it is anticipated that there will be reductions in harmful AOD use and associated health service utilisation, as well as significant improvements in personal goal achievement, quality of life, and treatment satisfaction. As the current study is the first stepped wedge cluster randomised trial of a compensatory CR intervention within a residential AOD population, the results potentially hold important implications for the way that interventions are delivered across treatment settings.

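### Client satisfaction is a secondary outcome for CR added to TAU, but no satisfaction measurement is scheduled in any TAU period

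*Protocol article*

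**What the plan says.** **The objective.** In the section The current study, the secondary outcomes are introduced with "The study will also assess the impact of CR in addition to TAU on a number of secondary outcomes", and client satisfaction is one of the seven items that follow. The Abstract likewise includes "client satisfaction with treatment" among the things CR may improve. The section Assessment measures repeats it: "Secondary outcome measures will evaluate substance use severity, health service utilisation, individual goal-attainment, quality of life, treatment satisfaction, and performance-based measures of EF". The Discussion anticipates, compared with pre-intervention, "significant improvements in personal goal achievement, quality of life, and treatment satisfaction", and Strengths and limitations states the same expectation again.

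**The schedule.** Table 2 has one row that names satisfaction with treatment, "Feasibility/satisfaction questionnaire (staff and clients". Its single mark is in the Post-trial column. The text gives this form no description and no outcome variable.

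**The nearest other instrument.** The Group Session Rating Scale (GSRS) is introduced with "The following scale will be administered at the end of each session during the CR phase". It is described as "designed to be a brief clinical tool to measure group-therapy alliance", and of its score the article says "The total score will be the process variable".

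**The concern.** A comparative outcome in a stepped-wedge trial needs the same measurement in control periods and in intervention periods. The randomised contrast then comes from sites that differ in condition within a period, and from each site before and after it crosses over. The stated objective and the expected improvement both call for such a contrast for satisfaction. The schedule in Table 2 does not provide the control-period half of it.

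The risk is in reporting. A satisfaction rating collected once, after all sites have changed to CR, would stand in the results beside outcomes that do have a randomised comparison. It could be read as an effect of CR when it only describes how respondents felt at the end.

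**Working it through.** The article gives no figure for satisfaction, so there is none to reproduce. The check sets the schedule against the objective.

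**Step 1. Which instruments could carry the outcome** (Table 2 and the descriptions of measures)

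| Instrument | Construct as described | When taken | Values in TAU |
|---|---|---|---|
| Feasibility/satisfaction questionnaire | Named for satisfaction; not described | Post-trial only | None scheduled within a TAU period |
| GSRS | Group-therapy alliance; process variable | During intervention, after CR sessions | None |
| Q-LES-Q-SF | Quality of life in daily functioning | Baseline, post-TAU/CR, follow-up | Yes, but for quality of life, which is a separate outcome |

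Only the first row is a measure of satisfaction with treatment.

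**Step 2. TAU and CR site-periods** (Table 1)

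| Period | Weeks | TAU sites | CR sites |
|---|---|---|---|
| 1 | 3–8 | 10 | 0 |
| 2 | 11–16 | 7 | 3 |
| 3 | 19–24 | 4 | 6 |
| 4 | 27–32 | 0 | 10 |
| Total | | 21 | 19 |

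Scheduled satisfaction measurements within TAU site-periods: 0 of 21.

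**Step 3. What the post-trial form could still give for TAU**

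From Period 4 every site delivers CR. A TAU client who is still resident has by then moved into a CR site-period, and one rating given after both conditions holds no separate TAU value. Clients with TAU only have left the service and must be traced.

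Post-trial is not defined, so I take a range. The early case is the start of Test Phase 5 (week 33) and the late case is the end of Test Phase 6 (week 42). Time since the site's last TAU period, with 52/12 = 4.33 weeks per month:

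| Sites | Last TAU week | Early case | Late case |
|---|---|---|---|
| 1–3 | 8 | 33 − 8 = 25 weeks (5.8 months) | 42 − 8 = 34 weeks (7.8 months) |
| 4–6 | 16 | 33 − 16 = 17 weeks (3.9 months) | 42 − 16 = 26 weeks (6.0 months) |
| 7–10 | 24 | 33 − 24 = 9 weeks (2.1 months) | 42 − 24 = 18 weeks (4.2 months) |

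The notes to Table 1 assume follow-up attrition of 65%, 75%, 85% and 90% at two, four, six and eight months. Taking the nearest time point, and assuming the form reaches people no better than follow-up does, expected loss is 85%, 75% and 65% for the three site groups in the early case, and 90%, 85% and 75% in the late case. For sites 4–10, clients who left after an earlier TAU period are further away still. Those who do answer have no earlier satisfaction value to compare with.

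**The case against.** Several points can be made for the plan, and some of them stand.

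- **A reader might infer that no comparison with TAU is possible at all.** The article does not support that. Table 2 does not restrict the questionnaire to people who received CR, and Post-trial is undefined. The same column holds individual time in treatment, which the Analysis plan compares across TAU and CR. That item can be taken from records, so it does not show that TAU clients receive the form, but it does show that the column is not reserved for CR. What can be said is that no satisfaction measurement is scheduled within a TAU period and that a late, selected response cannot carry the stepped-wedge contrast.
- **A reader might treat CR-only use of the GSRS as the error.** It is not. A rating of group alliance tied to CR sessions belongs only in CR, and the article calls it a process variable. Nor can GSRS data be said to come mainly from those who stayed longest, since the scale is completed after every session and includes people who leave later.
- **A reader might size the problem by the clients expected to leave before any CR.** That is the wrong measure. Many of them would leave during their first phase, and a form given at the end of the phase would largely miss them too.
- **The full protocol may describe the questionnaire.** It may, and the missing description is not the complaint. The article itself fixes the measurement times in Table 2, and these conflict with the objective it states. An analysis plan cannot supply values that were never collected.
- **The reach is small.** This is one of seven listed secondary outcomes. Neither primary outcome, the sample size nor the main model is affected.

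**Conclusion.** The contradiction between objective and schedule holds. Satisfaction is presented as an outcome of CR in addition to TAU, with an expected improvement over pre-intervention, yet it has no scheduled measurement in any of the 21 TAU site-periods and none at baseline. As scheduled, the outcome can describe acceptability at the end of the trial but cannot support the stated comparison.

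The count of 21 rests only on Table 1 as printed. The expected loss of 65% to 90% among TAU-only clients rests on the article's own attrition assumptions and on my range for the undefined post-trial date. It is an indication of how thin and selected such data would be, and the finding does not depend on it. The point merits correction but is confined to one secondary outcome.

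**What to change.** Choose one of two changes.

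1. **Keep the comparison.** Give the short client satisfaction form at each existing post-TAU/CR test phase, in both conditions, with items about treatment as a whole so that clients in TAU can answer them. Mark it in the Post-TAU/CR column of Table 2 and name its outcome variable. Analyse it with the stepped-wedge mixed model, using the period effects and the random effects for centre, time within centre and individual already planned for the BRIEF-A score. The staff part can stay post-trial. The cost is one short form at a visit that already takes place and slightly more respondent burden. The form will still miss clients who leave before the end of their phase.

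2. **Relabel.** Remove satisfaction from the CR-versus-TAU outcomes in The current study and Assessment measures, and from the expected improvements in the Abstract, the Discussion and Strengths and limitations. Report the post-trial form descriptively, as acceptability of CR, with the number approached and the number responding. The cost is wording only.

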#### Group Session Rating Scale (GSRS) [72]

The GSRS is a four-item visual analogue scale, designed to be a brief clinical tool to measure group-therapy alliance. The items are presented as bipolar anchors requiring a response on a ten centimetre line. The scale assesses aspects of individual’s perceptions of a group’s therapeutic environment, including; 1) the relationship between the leader and/or group, 2) goals and topics, 3) acceptability of the approach, and 4) overall fit. GSRS scores are obtained by measuring the marks made by the client and summing the lengths to the nearest centimetre on each of the four lines. Scores are summed out of a total possible score of 40. The total score will be the process variable.

#### Economic analysis

An evaluation of the cost of delivering CR versus TAU will be undertaken.

### Intake measures

The following data will be gathered on intake in the form of a structured questionnaireAge;Highest level of educational attainment;Employment status;Marital status;Number of Children/DependentsPrimary substance of misuse;Years of regular use (by substance);Nicotine UseUse of OSTRelapses in residential treatment;Relapses in community treatment;Abstinence duration;Country of birthFirst languageAustralian/Torres Strait Islander StatusReferral source (e.g. self-referred or court-ordered enrolment)

#### Drug and Alcohol Cognitive Impairment Screening Tool (DACIST) [73]

The DACIST was developed to measure self-reported historical factors that may reasonably contribute to cognitive impairment in a SUD population. Items assess history of head injury, overdose, seizures, hospitalization, foetal drug or alcohol exposure, neurological conditions, learning or behavioural difficulties during schooling and subjective appraisal of cognitive impairment.

#### Mini International Neuropsychiatric Interview V7.0.2 for DSM-5 (MINI) [74]

The MINI is a structured interview used for assessing indicators of DSM-5 diagnoses.

### Statistical methods

#### Sample size estimation

The primary outcome is the BRIEF-A GEC difference score between pre- and post-TAU/CR phase. Given previous data for a more comprehensive 24 h CR program [42], sample size calculations were based on a difference in BRIEF-A score of 2.25 for the current 12 h program. We used the sample size methodology for stepped wedge designs put forward by Hooper et al. [75]. Assuming a standard deviation of 5.15, obtained from the Marceau data [42], an individually randomised trial would require a total sample of 165 people in order to have 80% power to detect the intervention effect at the 5% significance level. The design effect for cluster randomisation, assuming an intraclass correlation of 0.05 and anticipating 20 people per cluster, is 1.95 and the design effect for repeated assessment, assuming a cluster autocorrelation of 0.5, is 0.534. The required number of clusters for this stepped wedge design is therefore nine. In order to account for a 10% loss of the total sample to follow-up, (e.g participants that are discharged and not replaced by new participants in the research) and to protect against the possibility of a cluster withdrawing from the trial, an additional cluster will be recruited yielding a total of 10.

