Site 8		TAU 1		TAU 2		TAU 3		Cog Rem 1		F/U Period	
Site 9		TAU 1		TAU 2		TAU 3		Cog Rem 1		F/U Period	
Site 10		TAU 1		TAU 2		TAU 3		Cog Rem 1		F/U Period	

Note: *Cog Rem* Cognitive Remediation Phase, *TAU* Treatment-As-Usual Phase, *F/U Period* Follow Up Period

The estimated number of participants is based on prior research in NSW residential drug and Alcohol Treatment [42]. *Discharge* refers to the discharge of participants from the residential treatment service (either through completing the program or self-discharge/drop out before the completion of the program). *Attrition* refers to drop-out from the study or otherwise being non-contactable following discharge from the treatment service.Each site will start with *n* = 20 participants on average;Within a single cohort, there will be:a 40% discharge rate over each six-week TAU/CR phase plus two-week test phase;a 65% discharge rate over the following 2 months;an 80% discharge rate over the following 4 months;a 90% discharge rate over the following 6 months; anda 95% discharge rate over the following 8 months;New clients will enter a service at the same rate as other clients leave the service;If a client enters a service during a TAU/CR phase, they will delay their participation in the trial until the next test phase;Some clients will participate in more than one CR phase;All participants who have completed at least one TAU/CR phase will be eligible for follow-up testing, which will occur at test phases 3, 4, 5 and 6.If a participant has had a CR phase they are ineligible for TAU follow-up.If a participant has had more than one CR phase they will still be eligible for CR follow-upFollow-up attrition rates have been estimated to be:65% attrition at two-month follow up75% attrition at four-month follow up85% attrition at six-month follow up90% attrition at eight-month follow up

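### The sample size counts 20 pre-post scores per site and phase with a 10% loss, but the protocol's own 40% discharge leaves about 12 to 13.6, so the method gives about 73-77% power with ten sites, not 80%.

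*Protocol article*

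**What the plan says.** All in the protocol article.

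- **Sample size estimation.** The outcome that is sized is a within-person change: "The primary outcome is the BRIEF-A GEC difference score between pre- and post-TAU/CR phase". The target is a difference of 2.25 with a standard deviation of 5.15. The requirement under individual randomisation is given as follows: "total sample of 165 people in order to have 80% power to detect the intervention effect at the 5% significance level". For clustering, the protocol applies a factor described thus: "assuming an intraclass correlation of 0.05 and anticipating 20 people per cluster, is 1.95". This is multiplied by 0.534 for repeated assessment (cluster autocorrelation 0.5), which gives nine clusters. A tenth is added: "In order to account for a 10% loss of the total sample to follow-up", with discharged and unreplaced participants as the example of such loss, and to protect against a site withdrawing.
- **Study design, list under Table 1.** Each site starts with 20 on average. Within a cohort the forecast is "a 40% discharge rate over each six-week TAU/CR phase plus two-week test phase". New clients arrive as fast as others leave, but those who enter during a phase are handled as follows: "they will delay their participation in the trial until the next test phase". Follow-up testing is open to people who have completed at least one phase.
- **Participants.** About 440 are to be recruited, with 40% expected to drop out within the first 8 weeks.
- **Analysis plan.** The GEC score is analysed in a linear mixed model with baseline GEC as a covariate and random effects for centre, time within centre and individual. Multiple imputation to include all participants is a sensitivity analysis.

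**The concern.** A change score needs the same person at both ends of a phase. The calculation counts 20 such scores per site and phase, while the forecast in the same article has 8 of every 20 leaving over the phase and the test phase that goes with it. Replacement keeps the next phase starting at 20, but it does not restore the lost pairs, because a mid-phase entrant has no score from the start of that phase. The 10% allowance therefore contradicts the 40% stated in two other sections. At stake is the 80% power for a primary outcome: a null result could be taken as well-powered evidence against a 2.25-point effect when the stated assumptions do not support that.

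**Working it through.** **Inputs from the protocol.** Difference 2.25, SD 5.15, 80% power, 5% significance (two-sided reproduces the stated figure), intraclass correlation (ICC) 0.05, cluster autocorrelation 0.5, m = 20 per site and period, four phases and three sequences (so K = 3 steps), 40% discharge per phase plus test phase.

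**1. The protocol's own figure.**

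- Individual randomisation: N = 4(1.960 + 0.842)² × 5.15² / 2.25² = 164.5 (stated 165).
- Clustering: DEc = 1 + (m − 1) × ICC = 1 + 19 × 0.05 = 1.95 (stated 1.95).
- Repeated assessment: r = m × 0.05 × 0.5 / DEc = 0.5/1.95 = 0.256. DEr = 3K(1 − r)(1 + Kr) / [(K² − 1)(2 + Kr)] = 9 × 0.744 × 1.769 / (8 × 2.769) = 0.534 (stated 0.534).
- Clusters: 164.5 × 1.95 × 0.534 / 20 = 8.6, rounded up to nine (stated nine).

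The arithmetic is right. The 0.534 is obtained with 20 outcome scores per site in each of four periods and no credit for repeated scores on the same person. So 20 is the number of analysable change scores that the calculation needs, not a count of residents in the house.

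**2. Pairs that the forecast leaves.**

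- Low end: 20 × (1 − 0.40) = 12.
- High end: the 40% covers eight weeks. If discharge is constant and everyone is tested exactly at week 6 (assumption), 20 × 0.6^(6/8) = 13.6.
- Consistency check: 440 = 200 + 3 × 80, that is, ten sites of 20 plus three refills of 40%. The recruitment forecast therefore matches 40% turnover per phase.

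**3. Same method with those counts.** Effective N = C × m / (DEc × DEr) for C sites; SE = 2 × 5.15 / √(effective N); power = Φ(2.25/SE − 1.96); detectable difference at 80% = 2.802 × SE.

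| Pairs per site-phase | DEc | DEr | Sites for 80% | Power, 10 sites | Power, 9 sites | Detectable, 10 sites | Detectable, 9 sites |
|---|---|---|---|---|---|---|---|
| 20 (as sized) | 1.95 | 0.534 | 8.6 | 85.7% | 81.9% | 2.08 | 2.20 |
| 18 (10% loss) | 1.85 | 0.539 | 9.1 | 83.5% | 79.5% | 2.15 | 2.26 |
| 13.6 | 1.63 | 0.551 | 10.9 | 76.7% | 72.2% | 2.35 | 2.47 |
| 12 | 1.55 | 0.556 | 11.8 | 73.2% | 68.7% | 2.44 | 2.58 |

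Example for 12 pairs and ten sites: 120 / (1.55 × 0.556) = 139.3; SE = 10.3/√139.3 = 0.873; 2.25/0.873 − 1.96 = 0.618; Φ(0.618) = 0.732.

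**4. Cross-check.** Generalised least squares (GLS) on site-period means with the actual 3/3/4 allocation and 12 pairs gives 73.5% with ten sites. With nine sites it gives 66-70%, depending on which sequence loses the site.

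**The case against.** **The planned model may be more efficient than the one sized.** This is the strongest point, and it stands in part. The Analysis plan adjusts for baseline GEC and includes an individual random effect; the calculation uses an unadjusted change score with no individual correlation.

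- *Baseline adjustment.* If 5.15 is the SD of the change score, pre and post variances are equal and the ICC is unchanged (all assumptions), adjustment scales the variance by (1 + ρ)/2, with ρ the pre-post correlation. By GLS with 12 pairs and ten sites, power is then 85%, 80% and 76% at ρ = 0.5, 0.7 and 0.9; with nine sites it is 81%, 76% and 71%.
- *Repeated scores on one resident.* If the 12 were a closed cohort, a correlation between change scores of 0.2 would give 77% and about 0.3 would reach 80% with ten sites. Turnover of 40% per phase reduces that gain: with overlap falling by 40% each phase, correlations of 0.3 to 0.7 give 76% to 82%.

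A reader might infer that the design cannot reach 80%. The document does not support that, because it gives none of these correlations. For the same reason it does not support 80%.

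**Twelve is not a figure the protocol states.** True. The 40% includes the two-week test phase, so some people may leave after their post-phase assessment; hence the range up to 13.6. The Abstract also describes inviting those expected to stay for the six weeks, although the Inclusion and exclusion criteria section invites everyone. Neither point removes the 40%, which the Participants section repeats.

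**The single extra site.** A reader might infer that it is spent twice, on the 10% loss and on a site withdrawal. At the protocol's own 10%, nine sites with 18 scores still give 79.5%, half a point short. That is not a separate defect; the fault is the 10%.

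**Imputation.** It appears only as a sensitivity analysis and does not restore outcome information that was never collected.

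**Conclusion.** The concern holds as an inconsistent input, not as an arithmetic slip. The formulas are applied correctly to a cluster size and a loss rate that the protocol's own forecast contradicts. With the protocol's method, ICC of 0.05 and cluster autocorrelation of 0.5, the shortfall from 80% is about 3 to 7 points with ten sites and 8 to 11 with nine. This rests on 12 to 13.6 paired scores per site-phase and on no credit for baseline adjustment or within-person correlation, as in the sample size section. The magnitude is sensitive to the ICC: with 12 pairs and ten sites, the GLS check gives 85% at an ICC of 0.01 and 63% at 0.10. What is established is that the stated calculation does not justify 80%. How much power the planned model would actually have cannot be computed from the document.

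**What to change.** In Sample size estimation:

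1. Reconcile the 10% loss with the 40% discharge in the Study design and Participants sections, and state that a mid-phase entrant adds no pre-post pair for the phase of entry.
2. Replace 20 per cluster by the expected number of paired GEC scores per site and phase (about 12, with the timing assumption stated if a higher number is used), and recompute both design effects.
3. Restate the power for 2.25 (about 73% with ten sites, 69% with nine), or restate the difference detectable at 80% (about 2.44 and 2.58).
4. If credit is taken for baseline adjustment or for repeated scores on the same resident, state the assumed correlation and its source, and show the power over a range.

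The cost is wording and a short recalculation. The stated power becomes less favourable unless item 4 can be justified. No sites, participants or assessments change.
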